### Sample size estimation and allocation

We previously reported the administration of 250 mg metformin per a day for 4 weeks reduced the number of ACF. In that trial, the mean number of ACF per patient decreased significantly from 8.8 ± 6.5 at baseline to 5.1 ± 5.0 at 4 weeks (*p* = 0.007) [28]. Although this study is exploratory research, and the accurate chemopreventive efficacy of montelukast is unknown, we assume that montelukast may have an effect that is equivalent to 60% of that observed for metformin on the reduction of ACF nubmer. Therefore, we estimate that the ACF number will change by about − 2 to − 3 on average. We determined that a sample size of 11–24 individuals in the LTRA group was needed to detect a significant reduction in the number of ACFs in the LTRA group using a paired t-test with a two-sided significance level of 5 and 80% power. Assuming some dropouts, we propose to recruit 30 participants in the LTRA group. To confirm that the number of ACF does not change during the study period, we propose to recruit 10 patients in the no treatment group after consecutively accumulating 30 patients in the LTRA group. Therefore, we propose to recruit 40 patients.

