### Statistical analysis

The change in the number of ACF, which is the primary endpoint, will be compared before and after the 8-week study period between the LTRA and no treatment groups by the paired *t*-test. Drug safety will be assessed by the chi-square test, and the remaining results will be compared by the *t*-test or Mann–Whitney *U* test between the two groups. *P* < 0.05 will be defined as statistically significant. All statistical analyses will be conducted using JMP® 15 software (SAS Institute Inc., Cary, NC, USA).

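### Ten untreated patients cannot confirm that ACF number is stable: the expected 95% interval is about ±2.3 to ±2.5 ACF, and the assumed drug effect is 2 to 3

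*Protocol article*

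**What the plan says.** All of this is in the Methods of the protocol article.

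- **Sample size estimation and allocation, drug effect.** In the earlier metformin trial "the mean number of ACF per patient decreased significantly from 8.8" (SD 6.5) to 5.1 (SD 5.0). Montelukast is assumed to have an effect "equivalent to 60% of that observed for metformin on the reduction of ACF nubmer", from which "we estimate that the ACF number will change by about" −2 to −3 on average.
- **Same section, LTRA group.** "We determined that a sample size of 11–24 individuals in the LTRA group was needed", "using a paired t-test with a two-sided significance level of 5 and 80% power". Then: "Assuming some dropouts, we propose to recruit 30 participants in the LTRA group".
- **Same section, no treatment group.** "To confirm that the number of ACF does not change during the study period, we propose to recruit 10 patients", enrolled after the 30 LTRA patients. No power, precision or margin is given for these 10.
- **Statistical analysis.** The primary endpoint is analysed with a paired t-test, worded both as before versus after and as between the groups. Other results use a t-test or Mann–Whitney test. P < 0.05 "will be defined as statistically significant". No criterion is given for concluding that the controls did not change.

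**The concern.** Confirming that a quantity does not change is a claim of equivalence. It needs either a margin or an interval narrow enough to rule out changes that matter. The article supplies neither, and the only tools it names are tests of difference. In a group this small, such a test can easily be non-significant when the count has really fallen.

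This matters because the LTRA group is sized for its own before-after comparison. Entry requires more than five rectal ACF, so a high count at baseline is part of selection and some regression to the mean is possible in both groups. The count made during the procedure is open-label, although a blinded recount from recordings is planned. The untreated patients are the main protection against reading such a fall as drug effect. If they are taken to have shown stability when they could not, that protection is weaker than it looks.

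**Working it through.** **Inputs from the article.** Controls n = 10; LTRA group n = 30; two-sided 5%; 80% power; assumed change 2 to 3 ACF. The 60%-of-metformin value is 0.6 × (8.8 − 5.1) = 0.6 × 3.7 = 2.22 ACF.

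**Input not in the article.** The SD of the within-patient change. It is an assumption here, recovered from the stated 11 to 24.

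**Step 1: reproduce 11 to 24.**

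- Normal approximation, n = (SD × (1.960 + 0.842) / δ)². With SD 3.45: δ = 3 gives 10.4, rounded up to 11; δ = 2 gives 23.4, rounded up to 24. Both stated figures are reproduced.
- Exact paired t (noncentral t). SD 3.3 gives 12 and 24. An SD just under 3.2 is needed to get 11 at δ = 3.

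The stated range is therefore coherent, with an SD of about 3.2 to 3.45 depending on the method.

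**Step 2: precision of the control mean change.** Half-width of the 95% interval = t(0.975, n − 1) × SD / √n.

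- n = 10, SD 3.2: 2.262 × 3.2 / 3.162 = 2.29
- n = 10, SD 3.3: 2.36
- n = 10, SD 3.45: 2.47
- n = 8 analysed: 2.365 × 3.2 / 2.828 = 2.68, rising to 2.88 at SD 3.45

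With an observed control change of exactly zero, the interval at n = 10 still contains −2 and −2.22. It does not contain −3.

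**Step 3: chance that a paired t-test in 10 controls misses a real fall** (1 − exact power).

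| True fall | Power, SD 3.2 | Power, SD 3.3 | Power, SD 3.45 | Missed |
|---|---|---|---|---|
| 2 | 42.3% | 40.2% | 37.4% | 58–63% |
| 2.22 | 49.9% | 47.6% | 44.3% | 50–56% |
| 3 | 75.1% | 72.6% | 68.8% | 25–31% |

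**Step 4: a larger SD.** With the metformin SDs and a before-after correlation of 0.5 (an assumption), the SD of the change is √(6.5² + 5.0² − 2 × 0.5 × 6.5 × 5.0) = 5.9. The half-width at n = 10 is then 2.262 × 5.9 / 3.162 = 4.2, and power is 16% for a fall of 2 and 30% for a fall of 3. Zero would no longer exclude −3.

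**Step 5: the between-group difference, 30 versus 10.** Half-width = t(0.975, 38) × SD × √(1/30 + 1/10) = 2.024 × SD × 0.365. This is 2.44 at SD 3.3 and 2.55 at SD 3.45. At those SDs, power is 37% and 34% for a difference of 2, and 68% and 64% for a difference of 3.

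**The case against.** Five points can be made for the plan.

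- **The rule is not stated.** A reader might infer that the plan treats P > 0.05 in the controls as proof of stability. The article does not say so. It gives a purpose and names no criterion. It also mentions a comparison between the groups, so it does not follow that the whole LTRA change would be credited to the drug. This stands. The fault is a stated purpose that nothing in the plan can meet, not a declared wrong rule.
- **The large end of the assumed range fares better.** It is tempting to say that 10 controls would confirm stability almost automatically, or could not exclude any change as large as the assumed effect. Neither is right for a fall of 3: at the back-solved SD the test would detect it 69 to 75% of the time, and an observed zero would exclude it. This stands and limits the point.
- **A 95% interval is stricter than a conventional equivalence test.** Two one-sided tests at 5% use the 90% interval, whose half-width at SD 3.3 is 1.833 × 3.3 / 3.162 = 1.91, so an observed zero would exclude −2.2. That is correct, but the observed mean will rarely be exactly zero. If the true change is zero, simulation puts the chance of showing equivalence within ±2.22 at only 24 to 33% for SD 3.45 to 3.2 (63 to 72% within ±3).
- **The SD is inferred.** True, hence the range. SDs above it make matters worse. The comparison of 10 with the plan's 11 to 24 needs no SD, though at the −3 end the shortfall is a single patient.
- **The study is exploratory and a pilot.** That can justify a small control group. It does not justify the word *confirm*.

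**Conclusion.** The point holds as a matter of what may be concluded from the controls. The article asks 10 patients to confirm stability, gives no margin or precision for it, and by its own calculation needs more patients than that to detect the change it assumes for the drug. Assuming an SD of change of 3.2 to 3.45, the control mean will be known to within about ±2.3 to ±2.5 ACF (±2.7 to ±2.9 with 8 analysed). A non-significant result would leave falls of 2 to 2.2 entirely plausible. A fall of 3 would be excluded only if the control mean came out close to zero.

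The between-group comparison does not remove the problem, being about as imprecise. Nor are the controls concurrent, since they follow the LTRA patients in time. Subtracting their change therefore does not remove drift in counting over calendar time.

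**What to change.** 1. In the sample size section, replace the stated aim of confirming no change with: to estimate how the ACF count changes over 8 weeks without treatment.
2. In the analysis section, add that the control mean change will be reported with its 95% interval, and that a non-significant control change will not be taken as evidence of stability.
3. Add that the LTRA-minus-control difference in change will be reported with its 95% interval. State the expected half-width (about 2.4 to 2.6 ACF) and that the controls are enrolled after the LTRA group, not alongside it.

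**Cost.** No extra patients or procedures. The claim becomes more modest. The trial is sized for the within-LTRA test, so the between-group estimate is imprecise (about 34 to 37% power for a difference of 2 at SD 3.3 to 3.45), and the protocol should disclose this.

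If the sponsor wants to keep the aim of showing stability, a margin has to be set and the control group sized for it. For 80% power with two one-sided 5% tests, a true change of zero and SD 3.3 to 3.45, that is about 25 to 27 controls for ±2, 21 to 23 for ±2.22, or 12 to 13 for ±3, before dropout.

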### Statistical analysis

The change in the number of ACF, which is the primary endpoint, will be compared before and after the 8-week study period between the LTRA and no treatment groups by the paired *t*-test. Drug safety will be assessed by the chi-square test, and the remaining results will be compared by the *t*-test or Mann–Whitney *U* test between the two groups. *P* < 0.05 will be defined as statistically significant. All statistical analyses will be conducted using JMP® 15 software (SAS Institute Inc., Cary, NC, USA).

### Trial steering committee and data monitoring committee

The Trial Steering Committee and Data Monitoring Committee will be located at the Y-NEXT. The Management Team will perform central monitoring of the trial status and data collection every month.

### Study flow

A study flow is shown in Fig. 1.

**Fig. 1 Fig1:**
[figure not shown]
Study flow chart

## Discussion

To the knowledge of us, this is the first clinical trial proposed to investigate the efficacy of LTRAs on colorectal ACF formation. LTRAs are broadly used for the treatment of allergic asthma and rhinitis [12, 13], and LTRAs are reported to decrease the risk of cancer in asthma patients in a dose-dependent manner [14]. Previous basic research has reported that CysLT_1_R is overexpressed in CRC and that montelukast induces the apoptosis of CRC cells [16, 17]. CysLTs have recently been focused on as significant regulators of gut homeostasis, with endogenous CysLT production mediating the proliferation and survival of gut mucosal cells [31].

Recent evidence focuses on the effect of leukotriene C_4_ (LTC_4_) in accelerating oxidative DNA damage, if not adequately repaired, can contribute to increase mutation rates and genomic instability [32]. DNA damage and genomic instability are major drivers of carcinogenesis [33]. CysLTs also acts as leukocyte chemoattractants. In addition, CysLT_1_ mediates Th17 cell migration, the storage of which associates with the progression of inflammation-associated cancers [34]. Chronic inflammation is a risk factor for cancer initiation and progression, as observed in patients with inflammatory bowel disease [35]. Furthermore, leukotriene D_4_ (LTD_4_) antagonists suppress chronic inflammation in a rodent model of acute enteritis and this may be effective in preventing inflammation-associated CRC [36]. LTRAs are leukotriene pathway inhibitors, and thus they may have potential as chemotherapy and/or chemoprevention agents to reduce the effect of leukotrienes. Previous in vivo studies have elucidated the chemopreventive effect of leukotriene pathway inhibitors [18, 19] and showed the potential use of LTRAs for chemoprevention. Therefore, we will conduct this trial to explore the chemopreventive effect of LTRAs in clinical setting.

This trial may have some limitations as follow. First, ACF are believed to be a fine surrogate biomarker of CRC, though its biological significance in humans is still controversial [20]. In CRC chemoprevention studies typically set the occurrence of adenomas or the CRC itself as endpoint of the study. Though the occurrence of CRC is the most appropriate endpoint, it is inappropriate for chemoprevention studies because CRC incidence rate is low in the general population and needed for long-term monitoring. Our group has previously reported that ACF is useful biomarker for CRC and conducted a chemoprevention study for colorectal ACF [25, 26]. Therefore, we designed this study using the number of ACF as the primary endpoint to investigate the chemopreventive effect of LTRAs. Second, an intervention duration of 8 weeks may be too short to reliably detect differences between two groups. Since, our group reported in a previous trial that oral administration of metformin for 4 weeks reduced the number of colorectal ACF in humans [28]. An intervention period of 8 weeks should be enough to assess the changes in the number of ACF, if LTRAs have a chemopreventive effect.

Our group previously conducted a short-term chemoprevention study of metformin for colorectal ACF and reported the preventive effect of the agent on the formation of ACF. Then we conducted a one-year metformin chemoprevention study for colorectal polyps. We propose to repeat the same steps as in our metformin study for the chemoprevention study using montelukast.

If LTRAs were proved to have efficacy for CRC prevention, the impact would be significant. Therefore, we believe it will be very interesting to assess whether LTRAs inhibit the formation of human colorectal ACF.

## Data Availability

The datasets used and/or analyzed during the current study will be available from the corresponding author on reasonable request.

## Abbreviations

CRC: Colorectal cancer
NSAIDs: Non-steroidal anti-inflammatory drugs
COX-2: Cyclooxygenase-2
LTRAs: Leukotriene receptor antagonists
CysLT_1_R: Cysteinyl leukotriene receptor
ACF: Aberrant crypt foci
YCU: Yokohama City University
UMIN: University hospital Medical Information Network
SSA/P: Sessile serrated adenoma/polyp
NCI-CTCAE: National Cancer Institute Common Toxicity Criteria for Adverse Events
PEG: Polyethylene glycol
AEs: Adverse events
LTC_4_: Leukotriene C_4_
LTD_4_: Leukotriene D_4_
